### Strategies to improve adherence to interventions {11c}

To ensure adherence to the prescribed intervention, specifically the administration of the initial dose of FSH, a designated study nurse will oversee and verify the correct dosing for each patient. Post-intervention, the treatment process will proceed as per routine clinical practice, without additional interventions made by the study team. The research team will ensure that the patient has adequate follow-up post-intervention in order to retrieve all relevant outcome data. This follow-up is in line with the standard care protocol for all IVF/ICSI patients, encompassing post-OPU medical visits, daily communication with the IVF laboratory team about the progress of in vitro culture, scheduling of the embryo transfer (whether fresh or frozen), and monitoring of any subsequent pregnancy. All relevant data will be tracked and recorded in the electronic medical records as part of routine clinical practice.

### Relevant concomitant care permitted or prohibited during the trial {11d}

Outside of first FSH dose allocation, the COS and IVF/ICSI treatments will be under control of the assigned clinician of the participant, as per routine practice.

### Provisions for post-trial care {30}

Care post-trial will follow routine practice and will be controlled by the assigned clinician for each participant.

In accordance with the Spanish legislation regarding clinical trials with medicines (Real Decreto 223/2004 6th of July), the sponsor of the study will subscribe an insurance covering the sponsor, investigator, collaborators, and center. This will cover any contingencies in the event of deleterious consequences for participants.

### Outcomes {12}

The primary efficacy criterion will be the number of mature, MII oocytes retrieved at OPU. This treatment outcome is the closest to the intervention and has a clear impact on IVF/ICSI cycle success. Secondary efficacy endpoints will include cycle cancelations (due to poor response or in the event that no mature oocytes are retrieved), OHSS risk, clinical pregnancy, and live birth per first transfer.

The following variables will be analyzed:Demographic variablesAge of the patient (years)AFCBMI (kg/m$$^2$$)AMH (ng/ml)Center of treatmentCOS outcome variablesNumber of MII oocytesNumber of cumulus-oocyte complexes (COCs)Estradiol at last ultrasound assessment (pg/ml)Number of follicles $$\ge$$ 11mm at last ultrasound checkOHSS risk ([yes/no]; risk is considered as present if estradiol > 5000 pg/ml and or $$\ge$$ 18 follicles $$\ge$$ 11mm at last ultrasound check)OPU cancelation ([yes/no]; present if COS is stopped prior to OPU)Cycle cancelation ([yes/no]; present if no MII oocytes are retrieved at OPU)Pregnancy outcome variablesClinical pregnancy ([yes/no]; present if positive fetal heart beat is observed at 7th week of gestation) per first embryo transferLive birth per first embryo transfer ([yes/no])

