### Criteria for discontinuing or modifying allocated interventions {11b}

Participants can withdraw from the study at any time and for any reason or no reason. The reason for withdrawal will be recorded if patients choose to disclose this information. Failure to administer the allocated FSH dose and discontinuation of IVF/ICSI for medical reasons will also result in withdrawal. Participants will be informed immediately regarding their withdrawal from the trial, if either an error in dose administration is detected or for a medical reason. If an error in FSH administration or medical reason is detected, the participant’s treatment will be interrupted or allowed to continue based on the clinical judgment of the healthcare provider. The data of withdrawn patients obtained during their participation in the study will be included in the study analysis. Withdrawn patients will not be replaced.

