**Assessments:**							
***Baseline variables***	✕	✕					
***Outcome variables***				✕	✕	✕	✕

A detailed description of the timepoints reflected in the figure is as follows:$$-t_1$$: First appointment with the clinician where information on IVF/ICSI treatment is relayed to the patient. Information on the trial is communicated to the patient, and informed consent documentation is handed over to eligible patients. If any of the baseline variables needed for IDoser to function (age, BMI, AFC, and AMH) are not available at this time, steps are put in place to obtain relevant information for the next appointment. These can include petition of blood tests for AMH level results, or echography for AFC assessment.$$t_0$$: Appointment with the clinician where the signed informed consent form is retrieved. Patient is included if all baseline variables are available. Once included, the participant is allocated to either the IDoser FSH selection group or control group. The FSH dose is prescribed to the participant.$$t_1$$: First day of the COS protocol. Participant will self-administer the prescribed dose of FSH.$$t_2$$: Last ultrasound appointment prior to OPU. First outcome variables are registered (OHSS risk and OPU cancelation).$$t_3$$: Day of OPU. Further outcome variables are registered (number of COCs recovered, number of MII recovered and cancelation after OPU).$$t_4$$: Appointment to evaluate the presence of a fetal heart beat at the 7th week of gestation to establish whether pregnancy is achieved after first embryo transfer in current IVF/ICSI cycle. Presence or absence of clinical pregnancy is registered.$$t_5$$: End of study, considered after outcome on live birth after first embryo transfer is obtained. Presence or absence of live birth achieved is registered.Baseline variables include all necessary variables required for IDoser, including age of the patient, BMI, AFC, and AMH levels.

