### Methods in analysis to handle protocol non-adherence and any statistical methods to handle missing data {20c}

Non-adherence to the trial protocol would imply that the participant has not received the intervention planned. These participants will be considered as having withdrawn from the trial. This per-protocol analysis strategy ensures that our study results accurately reflect the outcomes for those participants who fully adhered to the intervention protocol.

Missing covariates would immediately be considered as exclusion criteria, as they are necessary for the randomization and/or the use of the IDoser.

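### The primary endpoint is tied to OPU and sets no MII count for women whose stimulation is stopped before OPU, so the test as written would leave out failures that the assigned first dose can cause

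*Protocol article*

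**What the plan says.** Outcomes {12} defines the endpoint: "The primary efficacy criterion will be the number of mature, MII oocytes retrieved at OPU". The same section lists two separate yes/no variables. OPU cancelation is "present if COS is stopped prior to OPU". Cycle cancelation is "present if no MII oocytes are retrieved at OPU".

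The notes to Table 1 (Participant timeline {13}) put OPU cancelation at t2, the last ultrasound visit. The MII count comes later, at t3, the day of OPU: "Further outcome variables are registered (number of COCs recovered, number of MII recovered and cancelation after OPU".

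Statistical methods {20a} compares the MII count between arms by t test or Mann-Whitney test. Cancelations are compared separately by chi-squared test.

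Two sections bear on who is analysed:
- Section {11b}: "Failure to administer the allocated FSH dose and discontinuation of IVF/ICSI for medical reasons will also result in withdrawal". It adds: "The data of withdrawn patients obtained during their participation in the study will be included in the study analysis", and "Withdrawn patients will not be replaced".
- Section {20c} equates non-adherence with not having received the planned intervention, treats such participants as withdrawn, and says: "This per-protocol analysis strategy ensures that our study results accurately reflect the outcomes for those participants who fully adhered to the intervention protocol".

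No section gives an MII count to a woman who never reaches OPU.

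**The concern.** The Background {6a} says that the first dose recruits the follicles and that little can change the oocyte yield afterwards. Outcomes {12} names poor response as a reason for cancelation. A stop for response is therefore a possible effect of the randomised dose and should not be handled as incidental missing data. A mean taken only over women who reach OPU is a mean over a group selected after randomisation, partly by treatment.

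The endpoint is also uneven. A woman who reaches OPU and yields no mature oocyte scores an observed 0. A woman stopped earlier, possibly because she responded even less, has no score.

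Stimulation after the first dose is under the assigned clinician's control {11d}, and that clinician is not blinded {17a}. Cancelation could differ between arms for that reason too.

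At stake is the non-inferiority decision. If IDoser led to more response-related stops, part of its shortfall would be missing from the comparison with the 2-MII margin.

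**Working it through.** **1. The plan's own figure.** Inputs from Trial design {8} and Sample size {14}: margin 2 MII, SD 5.84, one-sided alpha 0.05, power 80%, drop-out 10%.

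n per arm = 2 × [5.84 × (1.645 + 0.842) / 2]² = 105.4, rounded up to 106. Then 106 / 0.90 = 117.8, rounded up to 118 per arm, or 236 in total. This matches the protocol, so the sample size is not in error. The issue is bias.

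**2. What is hidden.** Let p be the proportion stopped before OPU and m the mean MII among women with OPU, with subscripts C (control) and I (IDoser).

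- Deficit over all randomised women, counting a stop as 0: (1 − p_C)m_C − (1 − p_I)m_I
- Deficit seen in OPU-only data: m_C − m_I
- Hidden deficit = first minus second = p_I·m_I − p_C·m_C

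**3. Assumptions.** The protocol gives no mean MII and no cancelation rate. I assume p_C = 5%, m_C from 7 to 11, and p_I of 10% or 15%. The true all-patient deficit is set at the margin, 2 MII, so that m_I = (0.95·m_C − 2) / (1 − p_I). The standard error is taken at the planned evaluable number: 5.84 × √(2/106) = 0.802. The probability of falsely declaring non-inferiority is Φ(hidden / 0.802 − 1.645), which is 5% when nothing is hidden.

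| p_I | m_C | m_I | OPU-only deficit | Hidden | False non-inferiority |
|---|---|---|---|---|---|
| 10% | 7 | 4.65/0.90 = 5.17 | 1.83 | 0.17 | 7.5% |
| 10% | 11 | 8.45/0.90 = 9.39 | 1.61 | 0.39 | 12.3% |
| 15% | 7 | 4.65/0.85 = 5.47 | 1.53 | 0.47 | 14.5% |
| 15% | 11 | 8.45/0.85 = 9.94 | 1.06 | 0.94 | 31.9% |

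**4. When rates are equal.** With 5% stopped in both arms, equal OPU means of 6 to 10 and SD 5.84 among women with OPU, the probability of declaring non-inferiority is 0.82 with OPU-only data and 0.81 to 0.84 with zeros. The two analyses nearly agree.

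**5. Cost of counting zeros.** SD with zeros = √[(1 − p)·5.84² + p(1 − p)·m²]. Power with all 118 per arm analysed and no true difference = Φ(2 / [SD × √(2/118)] − 1.645).

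- p = 5%, m = 7: SD 5.89, power 0.83
- p = 10%, m = 11: SD 6.45, power 0.77

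**The case against.** Several points can be made for the protocol.

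**No sentence excludes these women.** A reader might infer that the plan removes them from the primary analysis. It does not say so. Section {11b} keeps the data obtained from withdrawn patients, and the hypothesis in {8} speaks of the average per group. A woman with no OPU has no oocytes retrieved, so a count of 0 is not ruled out. This stands. What remains is that {12} and {13} attach the count to OPU and nothing assigns a 0, so OPU-only analysis is the natural result of applying the plan as written.

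**The per-protocol rule does not remove them.** This also stands. Section {20c} concerns women who did not receive the planned intervention, which is the first dose. A woman who took that dose and was stopped later adhered.

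**The withdrawal rule may not cover them.** Whether a stop for poor response is a medical discontinuation under {11b} is arguable, since {12} treats it as an outcome. That conflict is a reason to reconcile the sections.

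**Cancelations are visible.** OPU without mature oocytes already scores 0, and OPU cancelation is tested between arms, so an imbalance would be reported. That test does not enter the non-inferiority decision.

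**The size is assumed and the direction is not fixed.** Agreed. Larger error rates follow if control cancelation is set to zero and the IDoser OPU mean is put at 7 to 11, but nothing in the protocol supports that. Under-dosing might also lower MII among women who reach OPU, which OPU-only data would show. If control cancels more, the bias runs against IDoser.

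**Coding could be left to a fuller document.** The protocol itself defines the endpoint, the withdrawal rule and the per-protocol strategy, and the gap arises from how they combine.

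**Conclusion.** The concern holds as a gap in the endpoint definition. Women stopped before OPU have no defined MII count, the planned test would omit them if run on the recorded counts, and {11b} and {20c} do not resolve their status. It does not hold as a claim that the protocol expressly excludes them, or that cancelations go unreported.

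The bias generally favours the arm that cancels more; strictly, it favours the arm with the larger product of cancelation rate and OPU mean. On the assumptions shown, 10% against 5% cancelation hides about 0.2 to 0.4 MII and raises false non-inferiority from 5% to about 8 to 12%. At 15% against 5% it hides about 0.5 to 0.9 MII, with false non-inferiority of about 15 to 32%. These are illustrations, because the document supplies neither input. With equal rates and equal OPU means there is almost nothing to correct. The change is still worth making: it is a matter of wording, and it removes a possible bias towards the conclusion the trial is designed to reach.

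**What to change.** 1. Define the primary outcome as MII oocytes obtained per randomised woman, with 0 when stimulation is stopped before OPU because of ovarian response or when no MII are retrieved.
2. Add a sensitivity analysis in which stops unrelated to response, such as personal reasons, are treated as missing and imputed.
3. Reconcile {11b} and {20c} so that a response-related stop counts as an outcome and not as withdrawal from the analysis.

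The cost is wording, and the protocol reports that recruitment had not started. The downside is a slightly larger SD, about 5.9 to 6.4 at 5 to 10% cancelation and OPU means of 7 to 11. If all 118 per arm are analysed, power is about 77 to 83%, so 236 remains roughly adequate.

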### Objectives {7}

This RCT tests the hypothesis that the performance of IDoser in prescribing the initial dose of FSH during COS is not inferior to the performance of a clinician in the average number of mature oocytes retrieved. Secondary objectives include the effect of IDoser on number of cycle cancelations (due to low response or no retrieval of oocytes), number of cases with OHSS risk, clinical pregnancy, and live birth per first transfer.

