### Trial design {8}

The trial design is a single-blinded RCT with two arms with a 1:1 allocation ratio, comparing outcomes following FSH dose selection by IDoser and dosing based on standard clinical practice.

The hypothesis that will be tested is whether the performance of IDoser selecting the first dose of FSH is non-inferior to the standard clinical protocol in regards to the average number of mature oocytes recovered per group. The difference in the number of MII that is regarded to be clinically significant is 2 MII. Our decision to consider a difference of two MII oocytes as clinically significant is based on empirical evidence and clinical relevance. As only 30 to 40% of inseminated mature oocytes develop into blastocysts [13, 14], the choice of two MIIs strikes a balance between statistical significance and clinical practicality, while taking into account the consequent impact on the success of fertility treatments. If the average number of MII in the intervention group is inferior in 2 or more units, IDoser will be considered inferior to the standard clinical practice.

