### Sample size {14}

A sample size calculation was performed to establish the number of participants required for the study. To determine a statistically significant difference equal or greater to 2 MII oocytes, 118 subjects are necessary in each group (*n *= 236), accepting an alpha risk of 0.05 and a beta risk of 0.2 in a one-sided test. We estimate a mean common standard deviation of 5.84 (as per the observational data included during development and validation of IDoser) and anticipate a drop-out rate of 10%.

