#### Univariable analysis

Differences regarding the number of MII oocytes amongst the groups will be evaluated using Student’s *t* test or Mann-Whitney *U* test (if the distribution is not normal). These tests will also be used to compare FSH doses and COC number.

Regarding all categorical variables (OHSS risk, OPU cancelation, cycle cancelation, clinical pregnancy, live birth), differences between groups will be evaluated using Pearson’s chi-squared. Description of adverse events (if any) will be provided by the study group.

Alpha risk is set at a 5% for the primary analysis, focusing on the difference between MII oocytes retrieved between the two arms of the study. For secondary and subgroup analysis, appropriate statistical adjustment methods will be implemented.

All analyses will be performed using Python version 3.7.6. A *p*-value < 0.05 will be considered as statistically significant.

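### Clinical pregnancy and live birth are compared per first embryo transfer, a denominator formed after randomisation that the allocated dose can change

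*Protocol article*

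**What the plan says.** The secondary endpoints in Outcomes {12} end with "OHSS risk, clinical pregnancy, and live birth per first transfer". The variable list in that section again defines both pregnancy outcomes per first embryo transfer, and the abstract and Objectives {7} agree. No section gives a version per randomised woman or says how a woman without a transfer is coded. Under Univariable analysis, one sentence covers every binary outcome: "Regarding all categorical variables (OHSS risk, OPU cancelation, cycle cancelation, clinical pregnancy, live birth" are all compared between groups by Pearson's chi-squared, with no denominator named.

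Cancellation is described in several ways. Objectives {7} speaks of the "number of cycle cancelations (due to low response or no retrieval of oocytes". The abstract and the endpoint text in Outcomes {12} refer to low or poor response, or to no *mature* oocytes. In the variable list, *cycle cancelation* is "present if no MII oocytes are retrieved at OPU". Stopping stimulation before pick-up is a separate variable, *OPU cancelation*, with no reason attached.

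**The concern.** Randomisation makes the two arms comparable as randomised. The women who reach a first transfer are a subset selected afterwards. If the dosing method changes who gets there, the two subsets differ in prognosis and in size, and a per-transfer test no longer estimates the effect of allocation. An arm with more cancelled cycles, or more cycles without a usable embryo, drops its failures from the denominator. Its per-transfer rate can then look equal or better while fewer of its randomised women have a baby. For a new dosing tool that is meant to be no worse than the clinician, that is the error to avoid.

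The cancellation issue is of a different and lesser kind. The stated endpoint and the variable of that name do not measure the same thing, so a reader could not tell which result answers the objective.

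**Working it through.** **1. The plan's own figure.** Inputs from Sample size {14} are "We estimate a mean common standard deviation of 5.84" and "accepting an alpha risk of 0.05 and a beta risk of 0.2 in a one-sided test". The margin comes from Trial design {8}: "The difference in the number of MII that is regarded to be clinically significant is 2 MII". With a true difference of 0, n per arm = 2 × (1.6449 + 0.8416)² × 5.84² / 2² = 2 × 6.1827 × 34.1056 / 4 = 105.43, so 106. Allowing for 10% drop-out, 106 / 0.9 = 117.8, so 118. This reproduces "118 subjects are necessary in each group". The calculation concerns MII oocytes only, and nothing below changes it. No figure is stated for the secondary outcomes.

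**2. Does reaching transfer depend on the allocated dose?** The article's own reasoning says it can.
- Background and rationale {6a}: the first dose recruits the follicles, and little can be done afterwards to alter the oocyte number.
- Outcomes {12}: the MII count clearly affects the success of the cycle.
- Trial design {8}: only 30-40% of inseminated mature oocytes become blastocysts. If oocytes are treated as independent (an assumption), the chance of no blastocyst is 0.6 to 0.7 with one MII, 0.36 to 0.49 with two, and 0.22 to 0.34 with three. These are not no-transfer rates, because day 3 transfer is allowed in specific cases. They show only that a low yield can remove a woman from the denominator.

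**3. A difference that per-transfer rates hide.** Live birth per woman = share reaching transfer × live birth per transfer. The article gives neither input, so both are assumed. Live birth per transfer is set at 35-45%, equal in both arms, so the per-transfer difference is 0 throughout.
- Equal shares: per-woman difference 0.
- 85% against 80%: 0.2975 − 0.2800 = 1.75 points at 35%; 0.3825 − 0.3600 = 2.25 points at 45%.
- 85% against 75%: 0.2975 − 0.2625 = 3.5 points at 35%; 0.3825 − 0.3375 = 4.5 points at 45%.

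**4. A difference that per-transfer rates create.** Assume instead that live birth per woman is equal in both arms, at 25-35%.
- 90% against 80% reaching transfer: 27.8% against 31.3% up to 38.9% against 43.8%, a gap of 3.5 to 4.9 points in favour of the arm with fewer transfers.
- 85% against 80%: a gap of 1.8 to 2.6 points.

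**5. Cancellation.** Let *a* be the share stopped before pick-up (assumed 2-10%, all for low response) and *b* the share of pick-ups with no MII (assumed 2-5%). The composite in the endpoint text is a + (1 − a)b, which runs from 0.02 + 0.98 × 0.02 = 4.0% to 0.10 + 0.90 × 0.05 = 14.5%. The variable named *cycle cancelation* captures only (1 − a)b, from 0.90 × 0.02 = 1.8% to 0.98 × 0.05 = 4.9% of randomised women.

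**The case against.** The wording may be meant to separate the first transfer from cumulative transfers. The timeline speaks of pregnancy following the first transfer in the current cycle, and an analysis plan could code women without a transfer as no event. That is possible. However, the abstract speaks of rates per first transfer, and every definition in the article points the same way.

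The size rests on assumed transfer shares and vanishes if they are equal. This stands. With about 106 evaluable women per arm and a rate near 36%, the standard error of a difference is √(2 × 0.36 × 0.64 / 106) ≈ 6.6 points, larger than any gap shown above. The trial is not powered for these outcomes on either denominator. That limits what can be detected, but it is no reason to choose the denominator open to bias. Reporting cancellations by arm would reveal part of the differential loss, but not loss from having no usable embryo.

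A reader might infer that every secondary comparison departs from the randomised groups. The article does not support that. OHSS risk, although it shares the quoted phrase, is assessed at the last ultrasound, and OPU cancelation can be scored for every stimulated woman. Cycle cancelation would be restricted to a subset only if it were limited to women reaching pick-up, which no section says. The two cancellation variables roughly match the two limbs of the endpoint, and both are tested. A reader might also infer that OPU cancelation mixes stops for low and for excessive response. The definition would allow it, but no section says that cycles are stopped for excessive response.

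**Conclusion.** The point holds for clinical pregnancy and live birth. Their stated denominator is fixed after randomisation and, on the article's own account of what the first dose does, plausibly affected by allocation. The direction cannot be predicted: a real per-woman difference can be hidden, or a spurious one created. The amounts in the working are illustrations under assumed rates, not estimates for this trial.

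Cancellation is a minor definition mismatch. Low-response stops fall outside the variable called cycle cancelation, stops before pick-up carry no reason, and Objectives {7} says oocytes where the abstract and Outcomes {12} say mature oocytes.

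Both matters concern secondary outcomes. The non-inferiority comparison of MII oocytes and its sample size stand as they are.

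**What to change.** - Make the between-arm comparison of clinical pregnancy and live birth from the first transfer per randomised woman, counting no transfer as no event. Keep per-transfer rates as descriptive, with the number reaching transfer shown by arm.
- Report the stated cancellation endpoint as one composite over all randomised women: stimulation stopped for low response, or no MII obtained. Tabulate stops for other reasons separately.
- Record the reason for stopping stimulation.
- Align the abstract, Objectives {7} and Outcomes {12} on one wording.

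Cost: the pregnancy outcomes need a change of wording and one more table, and the reported rates will be slightly lower. The cancellation composite needs a little more, because the variable list contains no reason for stopping; it should not be assumed that everything required is already collected. The sample size does not change. Trial status says recruitment had not started at the time of writing, so on that timetable the change could have been prespecified.
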